## Abstract

**Background:**

To investigate whether an exercise intervention using the VIVIFRAIL© protocol has benefits for inflammatory and functional parameters in different frailty status.

**Methods/design:**

This is a randomized clinical trial in an outpatient geriatrics clinic including older adults ≥60 years. For each frailty state (frail, pre-frail and robust), forty-four volunteers will be randomly allocated to the control group (*n* = 22) and the intervention group (*n* = 22) for 12 weeks. In the control group, participants will have meetings of health education while those in the intervention group will be part of a multicomponent exercise program (VIVIFRAIL©) performed five times a week (two times supervised and 3 times of home-based exercises). The primary outcome is a change in the inflammatory profile (a reduction in inflammatory interleukins [IL-6, TNF- α, IL1beta, IL-17, IL-22, CXCL-8, and IL-27] or an increase in anti-inflammatory mediators [IL-10, IL1RA, IL-4]). Secondary outcomes are change in physical performance using the Short Physical Performance Battery, handgrip strength, fatigue, gait speed, dual-task gait speed, depressive symptoms, FRAIL-BR and SARC-F scores, and quality of life at the 12-week period of intervention and after 3 months of follow-up.

**Discussion:**

We expect a reduction in inflammatory interleukins or an increase in anti-inflammatory mediators in those who performed the VIVIFRAIL© protocol. The results of the study will imply in a better knowledge about the effect of a low-cost intervention that could be easily replicated in outpatient care for the prevention and treatment of frailty, especially regarding the inflammatory and anti-inflammatory pathways involved in its pathophysiology.

**Trial registration:**

Brazilian Registry of Clinical Trials (RBR-9n5jbw; 01/24/2020). Registred January 2020. http://www.ensaiosclinicos.gov.br/rg/RBR-9n5jbw/.

## Background

Frailty is a biological syndrome characterized by a reduction in physiological reserves and a decrease in resistance to stressors [1, 2]. The worldwide prevalence of frailty is 4–16% over 65 years old and 25% in those aged 85 or older [3, 4]. Frailty is characterized as a main cause of death in seniors [5] and significantly increases the risk of falls, disability, hospitalizations and long-term care [6]. According to the theoretical model of the frailty phenotype, a multisystemic impairment of homeostasis trigger a cascade of dysregulation during the aging process, causing a cycle of energy reserve reduction [1, 2, 7]. Physical frailty is the biological model most used for diagnosis and is composed by three or more among five components (unintentional weight loss, self-reported fatigue, low handgrip strength, low physical activity; and low walking speed). Pre-frailty is identified by one or two of these components [2].

Chronic inflammation is a key element in its pathophysiology [7] and has its origin through factors that include aging changes, genetic and metabolic variations, environmental stressors, lifestyle, and chronic and acute diseases. Frail individuals have higher levels of inflammatory mediators, such as C-reactive protein (CRP), tumor necrosis factor alpha (TNF-α) and interleukin-6 (IL-6) directly influencing frailty onset by degrading proteins, or indirectly, affecting the functioning of metabolic pathways [8, 9]. Low-grade inflammation is associated with decreased strength and muscle mass, its intensity is inversely proportional to the practice of muscle strengthening activity and can be reduced with resistance training [10, 11].

Few controversial studies investigated the effect of exercise on inflammatory biomarkers in frailty. A stabilization of IL-6 and CRP was observed in frail and pre-frail older persons during physical training and nutritional support, while controls presented an increase in these cytokines [12]. Moreover, those who improved physical performance lowered IL-6 levels. In another study, a resistance training for knee flexors and extensors muscles did not influence low-grade inflammation in older adults. However, plasma levels of TNF type 1 receptors were inversely related to the muscle strength at the end of 12-weeks [13]. In youngers, the increase in the serum level of TNF-α after intervention correlated with reductions in muscle mass after a 4-week follow-up period, suggesting that TNF-α may play a role in muscle loss due to detraining [14]. Collectively, these studies show the potential anti-inflammatory role of physical activity.

Thus, this single-center parallel randomized controlled trial will allow to investigate whether a low-cost multicomponent exercise program called VIVIFRAIL© [15, 16] has benefits for reducing inflammation and improve the functional status among older persons with different frailty status. This program is performed according to the functional capacity and has been demonstrated to be a safe and effective to reverse the functional decline associated with acute hospitalization in seniors [17, 18]. The specific objectives of this RCT will be evaluate the effectiveness of the VIVIFRAIL© [15, 19] program with respect to the concentration of inflammatory and anti-inflammatory mediators and in the functional status of older persons in the different frailty status during 12-weeks. It is hypothesized that older persons submitted to the VIVIFRAIL© exercise protocol will present a decrease in serum levels of pro-inflammatory interleukins, associated with an increase in serum levels of anti-inflammatory interleukins and, secondarily, an improvement in the functional status is expected.

## Methods/design

### Design and participants

The present study is a single-center parallel randomized controlled trial comparing a multicomponent physical activity (i.e. VIVIFRAIL©) to usual health promotion. Participants are older adults from the Geriatrics Outpatient Center of Jundiaí Medical School, State of São Paulo, southwester of Brazil. These patients usually come from primary care centers or access the geriatric outpatient care directly.

Volunteers who meet the inclusion criteria will be randomly allocated to the intervention or control groups by an independent person, who is blind to their clinical data or frailty status. The data for participants in both groups will be obtained at three different times: at the beginning of the study, at the end of the study and after 3 months after the end of the intervention. The study flowchart is illustrated in Fig. 1. This study protocol follows the standard protocol for clinical trials in accordance with the SPIRIT2013 statement and follows the CONSORT statement for clinical trial transparency [20, 21]. The study is registered on the Brazilian Registry of Clinical Trials (REBEC) platform under the license RBR-9n5jbw. The study was approved by the Research Ethics Committee of the Jundiaí Medical School. For any ancillary study that data collection/request is not covered in the original informed consent process for this main trial, another signed consent will be obtained from every participant.

**Fig. 1 Fig1:**
[figure not shown]
CONSORT Fluxogram showing the study design and the flow of participants

### Recruitment and inclusion criteria

The initial recruitment will be carried out with all older adults who followed up at the clinic during the year of 2019. The older adults that are receiving care at the clinic, that are aged 60 years or older, and who have signed the informed consent will be included in the study. The exclusion criteria will be: probable cognitive impairment identified using the 10-point cognitive screening instrument (10-CS) with a final score of 0 to 5 points; any contra-indication for the VIVIFRAIL© [19] (Table 1), life-expectancy less than 12 months, permanent or temporary inability to walk; localized loss of strength and aphasia due to severe stroke; severe impairment of motor skills, speech or affectivity associated with Parkinson’s disease in an advanced/unstable stage; severe hearing or vision deficits; cancer and autoimmune diseases in activity; cancer in the last 3 years; inability to perform the Short Physical Performance Battery (SPPB); limb amputation; and physical activity or physical therapy in the last 6 months.

**Table 1 Tab1:** Absolute and relative contraindications for physical activity according to VIVIFRAIL©Protocol

VIVIFRAIL© Contraindications	
Absolute	• Acute heart attack (recent 3–6 months) or unstable angina; • uncontrolled atrial or ventricular arrhythmias; • aortic dissecting aneurysm; • severe aortic stenosis; • acute endocarditis / pericarditis; • uncontrolled high blood pressure (> 180/100 mmHg); • acute thromboembolism; • acute or severe heart failure; • acute or severe respiratory failure; • uncontrolled postural hypotension; • uncontrolled acute decompensated diabetes mellitus or low blood sugar; • a recent fracture in the last month (strength training); • any other circumstance the doctors believes prevents doing physical activity
Relative	• A recent fracture in the last 3 months (strength training) • Infections that affect one’s general condition • A pathology that causes serious functional limitation (Barthel scale of less than 20)

Those who meet the inclusion criteria and agree with the study criteria presented by the researcher carrying out the recruitment (a medical doctor or physical therapist) will sign the consent information term and will be submitted to the assessment of the Frailty Physical Phenotype criteria proposed by Fried and colleagues (2001), according to the description below:

- Fatigue: it will be evaluated through self-report using questions 7 and 20 of the Center for Epidemiological Studies - Depression (CES-D) scale. The volunteers will be asked about the frequency in which they perceived to make an effort to perform usual tasks and the frequency with which they were unable to carry out their activities in the last week. Positive affirmation “most of the time” or “always” in any of the two questions will be considered a manifestation of fatigue.

- Unintentional weight loss in the last year: older person with unintentional weight loss greater than 5% of body weight will be scored according to this criterion, adjusted for sex and body mass index (BMI).

- Hand grip strength will be performed using a manual hydraulic dynamometer (Jamar hand dynamometer, model J00105, Lafayette Instrument Company, Lafayette, Lousiania, USA). This instrument is composed of a closed hydraulic system that measures the amount of force produced by an isometric contraction applied over its loops, and the hand grip is recorded in kilogram-force. It will be performed with the individual sitting in a chair without armrests and with their feet resting on the floor, with adducted shoulder, the elbow flexed at 90°, the forearm in neutral position and the wrist between 0 and 30° in extension. Prior to the evaluation, the volunteer will be familiarized with the instrument for the opportunity to handle the dynamometer before recording the measurements and will be guided on the evaluation procedure. The volunteer will be instructed to tighten the dynamometer handle tightly held by the volunteer’s dominant hand and verbal commands will be provided to encourage volunteers to produce maximum grip strength. Three evaluations will be carried out, with a one-minute rest between each one and the average of the repetitions, in kilogram-force (kgf), will be used for statistical analysis. Low grip strength will be indicated by the average values ​​interpreted according to sex and BMI. For females, will be considered low handgrip strength values ≤17 kg for those with BMI ≤ 23 kg / m^2^, values ≤17.3 kg for a BMI between 23.1–26 kg / m^2^, values ≤18 kg for a BMI between 26.1–29 kg / m^2^ and values ≤21 kg for females with BMI > 29. For males, will be considered a low hand grip strength values ≤29 kg for those with BMI ≤ 24 kg / m^2^, values ≤30 kg for a BMI between 24, 1–26 kg / m^2^, values ≤30 kg for a BMI between 26.1–28 kg / m^2^ and values ≤32 kg for males with BMI > 28.

- Low gait speed: it will be assessed when asking the older person to walk at their usual speed for 4.6 m, repeating the route 3 consecutive times. The average speed obtained in each of the routes will be interpreted according to the height and gender of the participants. Will be considered with low gait speed the male participants with a height ≤ 173 cm who took a time ≥ 7 s or those with height > 173 cm who took a time ≥ 6 s. For females’ participants, will be considered with low gait speed those higher than 159 cm who took ≥7 s or those higher than 159 cm who took a time ≥ 6 s to complete the test.

- Low level of physical activity: Low physical activity is defined as spending less than 383 cal per day for males and 270 cal for females, corresponding to the lowest quintile of energy expenditure in the older population. The energy expenditure will be measured with some items of the Minnesota Leisure Activity Questionnaire, which has been translated and validated in Portuguese [22]. Based on self-report frequency and duration of physical activities (including sports and leisure activities), the calculation of caloric expenditure will be performed by multiplying the metabolic equivalent of the task (MET) of each activity by the body weight (Kg), time (minute) and the predetermined measure of 0.0175.

After evaluating the Frailty Physical Phenotype criteria, participants who have 1–2 of these components will be considered as pre-frail, 3 or more components as frail, and those without any as robust.

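### The women's slow-gait rule names the same height band twice and gives no cut-off at 159 cm or below, so some shorter women are placed one frailty group too low

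*Protocol article*

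**What the plan says.** The low gait speed bullet in the Protocol article (Recruitment and inclusion criteria) times a usual-pace walk over 4.6 m and states that the result "will be interpreted according to the height and gender of the participants".

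- Men: slow gait applies to "the male participants with a height ≤ 173 cm who took a time ≥ 7 s or those with height > 173 cm" at 6 s or more.
- Women: the rule reads "will be considered with low gait speed those higher than 159 cm who took ≥7 s or those higher than 159 cm"; the second of these two clauses carries a time of 6 s or more.

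The same section says that the frailty phenotype is assessed by the description that follows it, so this bullet is the working definition. It closes with the grouping rule: "participants who have 1–2 of these components will be considered as pre-frail, 3 or more components as frail, and those without any as robust".

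Allocation, described under Randomization and blinding, is 22 participants per arm within each of the three frailty groups. The Abstract gives 44 per frailty state.

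**The concern.** A height-dependent cut-off needs bands that do not overlap and that together cover every height. The women's rule fails on both counts: one band appears twice with different times, and the other is absent. No other part of the article gives a gait cut-off for women.

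Slow gait is one of the five components whose count sets frail, pre-frail or robust. That status is the randomisation stratum, the recruitment quota and the subject of the trial's question about different frailty states. A wrong threshold here can therefore change which group a participant enters, and that is hard to undo after allocation. Two assessors could also fill the gap differently, or score the item as absent for every shorter woman.

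**Working it through.** The article states no figure to reproduce, so the check applies the printed rule literally and then follows it through the component count.

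**Step 1. The two rules side by side** (both from the low gait speed bullet)

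| Sex | 7 s clause applies to | 6 s clause applies to | Heights with no clause |
|---|---|---|---|
| Men | 173 cm or less | above 173 cm | none |
| Women | above 159 cm | above 159 cm | 159 cm or less |

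**Step 2. The women's rule applied literally**

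| Height | Under 6 s | 6 s to under 7 s | 7 s or more |
|---|---|---|---|
| Above 159 cm | not slow | slow (6 s clause only) | slow (both clauses) |
| 159 cm or less | no clause | no clause | no clause |

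Above 159 cm, whoever meets the 7 s clause already meets the 6 s clause, so the 7 s clause does no work. At 159 cm or less the item cannot be scored at any time, and the maximum count is 5 − 1 = 4.

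**Step 3. When the gait item changes the frailty group**

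The other four components have 2⁴ = 16 yes/no patterns. The number of patterns with k positive is C(4, k). Groups are 0 = robust, 1–2 = pre-frail, 3 or more = frail.

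| Other components positive (k) | Patterns | Group if gait is not scored (k) | Group if gait is scored (k + 1) | Changes? |
|---|---|---|---|---|
| 0 | 1 | robust | pre-frail | yes |
| 1 | 4 | pre-frail | pre-frail | no |
| 2 | 6 | pre-frail | frail | yes |
| 3 | 4 | frail | frail | no |
| 4 | 1 | frail | frail | no |

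The item is decisive in 1 + 6 = 7 of 16 patterns. The patterns are not equally likely, so 7/16 is not a share of women.

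**Step 4. Who is actually moved**

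A woman changes group only if all three conditions hold: she is 159 cm or shorter, she would be slow under the intended cut-off, and she has exactly 0 or 2 other components. The documents give none of the three frequencies. Where a change occurs, it is always one group and always towards less frail.

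**Step 5. What the rule does not enter**

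- Sample size (Statistical analyses): 18 per group comes from a 30% fall in IL-6 at 80% power and 5% error, raised to 22 for drop-out. No gait cut-off is used.
- Arm comparison: classification comes before allocation, and allocation is 1:1 within each frailty group. A misplaced woman is equally likely to enter either arm of the stratum in which she is placed.
- Exercise programme: this is chosen from the SPPB and the 6-m gait test (Intervention group), not from this item.

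**The case against.** The best defence is that this is a slip of a few characters with an obvious anchor. The article names a published phenotype as its source, the men's rule shows the intended structure, and the text says that results depend on height. The article is also condensed, and nothing shows that the printed wording was the rule used at screening. This stands as a limit on the harm that can be inferred: if the screening form carries a complete rule, only the published text needs correcting. It does not remove the error. The article states a rule rather than leaving one to a fuller document, and the text alone does not settle which clause is misprinted.

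Three stronger readings are tempting, and the documents do not support them.

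- *A woman above 159 cm who takes 6 to 7 s is both slow and not slow.* The clauses are joined by *or*, so either is sufficient. She meets the 6 s clause and is slow. The clear gap is at 159 cm or less.
- *Some 20–42% of participants are misclassified.* Assuming that 50–70% of the 132 participants are women and that 40–60% of those are 159 cm or shorter gives 132 × 0.5 × 0.4 ≈ 26 to 132 × 0.7 × 0.6 ≈ 55. Neither share is in the documents. The range also counts every shorter woman, including brisk walkers and those with 1, 3 or 4 other components, whose group does not change.
- *The sizing, the allocation or the treatment effect is compromised.* The sample-size inputs do not involve this rule, and error made before 1:1 allocation within strata does not favour an arm.

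**Conclusion.** The rule is wrong as written and should be corrected. It is a decision threshold for group membership, so it is more than a background typing error. Under the literal reading, shorter women who walk slowly and have exactly 0 or 2 other components are placed one group too low. The number cannot be derived from the documents.

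The damage is to meaning. The robust and pre-frail strata may contain women who belong one group higher, and the quotas of 44 are then filled by a different population from the one described. Results by frailty state become harder to interpret and to replicate. The randomised comparison within each stratum stays valid for the women placed in it.

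This conclusion assumes that the printed wording was, or could be, applied as it stands. It also takes the statement that gait is interpreted by height to mean that shorter women were meant to have a cut-off.

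**What to change.** 1. Reconcile the two women's clauses with each other, with the phenotype definition cited in Recruitment and inclusion criteria, and with the form used at screening, so that every height has exactly one applicable cut-off. No value is proposed here; the source definition has to settle it.
2. Correct the protocol text, and the screening form if it carries the same wording.
3. Re-check the frailty group of any woman classified under the printed wording. The ones whose group can change are those for whom the corrected rule alters the gait item and who have exactly 0 or 2 other components.
4. If any such woman has already been randomised, keep her allocation, document the discrepancy, and report her group under both the printed and the corrected rule.

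The cost is a one-line correction plus a limited check of recorded heights, walk times and component counts. If the form already held a complete rule, only the text changes.

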#### Intervention group

The VIVIFRAIL© [15, 19] multicomponent exercise intervention protocol was developed in Europe (Erasmus+programme, European Union) and consists of resistance training, gait retraining, and balance training. Different functional capacity levels will be determined based on the scores obtained from the SPPB and the 6-m gait velocity test, with each leading to the recommendation of a certain customized multicomponent physical exercise program (Program A, B, C1, C2 or D). These programs are composed by arm and leg strength and power exercises, balance and coordination to prevent falls, flexibility and cardiovascular endurance exercises [15, 19].

After the initial assessment and categorization of the volunteer in any of the physical exercise programs, a multicomponent program will be carried out for 12 weeks, totaling 60 sessions. Two weekly supervision sessions will be held, lasting 60 min each, with an interval of 1 day between them. Participants will receive the materials (elastic bands, towel and bottles with water/sandy) to perform the exercises and will be trained to perform exercises individually at home with a frequency of 3 days a week, in order to complete 5 days of activity per week. Instructions will be properly adapted to the focused population and will be provided to the volunteers in the Portuguese language.

The VIVIFRAIL© program is composed by arm and leg strength and power exercises, balance and coordination to prevent falls, flexibility and cardiovascular endurance (i.e walking) exercises [16, 30]. The proposed exercises’ sets and repetitions, intensity of progression of each Program are shown in Table 3 and illustrated in Fig. 2.

**Table 3 Tab3:** Proposed exercises sets, repetitions (Reps) and intensity (Intst) of progression of each program of the VIVIFRAIL© multicomponent exercise methodology

		Program A	Program B		Program C 1 and C2	Program D
**Resistance training**	Sets / Reps	Week 1–2: 2 sets / 10 reps Week 3–4: 2 sets / 10 reps Week 5–6: 2 sets / 10 reps Week 7–8 2 sets / 10 reps Week 9–10: 2 sets / 10 reps Week 11–12: 2 sets / 10 reps	Week 1–2: 2 sets / 10 reps Week 3–4: 2 sets / 12–15 reps Week 5–6: 3 sets / 12 reps Week 7–8 2 sets / 10 reps Week 9–10: 2 sets / 12–15 reps Week 11–12: 3 sets / 12–15 reps			
	Intst	Determine the weight that allows to do the exercise properly without stopping yet makes feel as though they have made an effort by the end: Week 1–6: 30 times Week 6–12: 20 times				

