**Cardiovascular training**	Sets / Reps	Time walking / rest / times Week 1–4: 5–10s / 10s / 5–7 Week 5–6: 10–15 s / 20s / 5–7 Week 7–8: 15–30s /20s / 5–10 Week 9–10: 30–45 s / 20s / 5–10 Week 11–12: 45–60s /20s/12–15	Time walking / rest / times Week 1–4: 20s / 10s / 5–7 Week 5–6: 20–25 s / 20s / 5–7 Week 7–8: 25–35 s /20s / 5 Week 9–10: 45 s / 20s / 5 Week 11–12: 50–70s /20s/12–15	Time walking / rest / times		Time walking / rest / times Week 1–2: 15 min / 30s / 2 Week 3–4: 15 min / 30s / 3 Week 5–6: 20 min / 30s / 2 + 15 min Week 7–8: 30-35 min /30s / 2 Week 9–10: 50–70 min Week 11–12: 50–70 min
				C1	Week 1–2: 3-5 min / 30s / 2 Week 3–4: 5 min / 30s / 2 Week 5–6: 5 min / 30s / 3 Week 7–8: 5-7 min /30s / 3 Week 9–10: 7–12 min Week 11–12: 12–20 min	
				C2	Week 1–2: 8-10 min / 30s / 2 Week 3–4: 10 min / 30s / 2 Week 5–6: 5-10 min / 30s / 3 Week 7–8: 15-25 min Week 9–10: 25–30 min Week 11–12: 30–40 min	
	Intst	Usual walking pace				
**Balance training**	Sets / Reps	Remain in the same position, and do 2–3 times with each leg, counting to: Week 1–2: 5–10 Week 3–4: 10 Week 5–6: 15 Week 7–8: 20 Week 9–10: 25 Week 11–12: 30	Remain in the same position and do 2–3 times with each leg, counting to: Week 1–2: 10 Week 3–4: 15 Week 5–6: 20 Week 7–12: 30 + Walk 10 steps/ 2 times + Walk in a relaxed way and step over 5 obstacles / 8 times	Remain in the same position counting to: Week 1–2: 10 Week 3–4: 15 Week 5–6: 20 Week 7–12: 30 These exercises will be done 2 times with each leg, followed by: Walk 10 steps/ 2 times + Walk in a relaxed way and step over 5 obstacles / 8 times		
**Flexibility**	Intst	-Change the position of the arms; -Cross your arms - Use of different surfaces - Eyes closed.				
	Sets / Reps	Week 1–6: 2 sets of 3 reps Week 7–12: 3 sets of 3 reps				
	Intst	Remain in the same position for 10–12 s

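### The low-activity frailty cut-off is printed as a daily total, which under the protocol's own energy formula does not fit its description as the lowest fifth of older people

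*Protocol article*

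**What the plan says.** All of the following is in the protocol article, Recruitment and inclusion criteria, unless noted.

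- The cut-off: "Low physical activity is defined as spending less than 383 cal per day for males and 270 cal for females". The period is written once, before the male figure, and carries over to the female figure by implication.
- Its meaning: "corresponding to the lowest quintile of energy expenditure in the older population".
- What is counted: "The energy expenditure will be measured with some items of the Minnesota Leisure Activity Questionnaire".
- How it is computed: "multiplying the metabolic equivalent of the task (MET) of each activity by the body weight (Kg), time (minute) and the predetermined measure of 0.0175".
- How it is used: "participants who have 1–2 of these components will be considered as pre-frail, 3 or more components as frail, and those without any as robust".

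The allocation step (section Randomization and blinding) then puts 22 people from each frailty group in each arm, so 44 people with no component at all must be found for the robust stratum.

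**The concern.** The period, the formula and the percentile claim are three statements about one number, and they do not appear to agree. If the cut-off marks the lowest fifth, four in five older people must exceed it. A daily total of 383 or 270 from leisure items alone looks far too demanding for that.

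The criterion is one of the five components that form the strata, and the trial asks about effects in frail, pre-frail and robust people. A cut-off set too high adds a component wrongly, and at two points on the count one extra component changes the stratum. Stratum-specific results would then describe populations other than the ones named.

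**Working it through.** **Inputs from the protocol.** Cut-offs 383 (men) and 270 (women) per day; energy = MET × kg × min × 0.0175; strata at 0, 1–2 and 3 or more components.

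**Assumptions.** The protocol gives no MET values, body weights or expenditure distribution. I take 60–80 kg and 2.5–4 MET, and then widen the weights.

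**The plan's own figure.** The 383/270 cut-off cannot be reproduced as a 20th percentile because no distribution is given. What can be checked is whether a daily period is compatible with that description.

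**Step 1: energy scale.** One MET for 24 hours at 70 kg gives 1 × 70 × 1,440 × 0.0175 = 1,764, a sensible resting day in kcal. The formula therefore yields kcal, while the cut-off is printed in cal. The same check shows that total expenditure cannot be what is meant. At 60 kg, rest alone gives 60 × 1,440 × 0.0175 = 1,512, so nobody would fall below 383. Only the questionnaire activities can count.

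**Step 2: minutes needed every day.** Minutes = cut-off ÷ (MET × kg × 0.0175).

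| Case | kcal/min | Minutes per day |
|---|---|---|
| Man, 70 kg, 3.5 MET | 4.29 | 383 / 4.29 = 89 |
| Man, 60 kg, 2.5 MET | 2.625 | 383 / 2.625 = 146 |
| Man, 80 kg, 4 MET | 5.60 | 383 / 5.60 = 68 |
| Woman, 60 kg, 3.5 MET | 3.675 | 270 / 3.675 = 73 |
| Woman, 60 kg, 2.5 MET | 2.625 | 270 / 2.625 = 103 |
| Woman, 80 kg, 4 MET | 5.60 | 270 / 5.60 = 48 |

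With wider weights (men 60–100 kg, women 50–90 kg) the ranges are 55–146 and 43–123 minutes. For the printed cut-off to be a lowest quintile, 80% of older people would have to do more than this every day in the listed activities.

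**Step 3: the same figures as weekly totals.** 383 per day is 383 × 7 = 2,681 per week, and 270 per day is 1,890 per week, so the readings differ by a factor of 7. Read per week, the 70 kg man needs 89 / 7 ≈ 13 min/day and the 60 kg woman 73 / 7 ≈ 10 min/day.

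**Step 4: effect of one wrongly added component.**

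| Other components | Stratum without it | Stratum with it |
|---|---|---|
| 0 | robust | pre-frail |
| 1 | pre-frail | pre-frail |
| 2 | pre-frail | frail |
| 3 or 4 | frail | frail |

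The robust stratum can only lose people and the frail stratum can only gain them. The robust target is 2 × 22 = 44.

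**The case against.** **It may be a misprint.** The period appears once, the protocol says it follows a published phenotype, and the adjacent gait item has an evident slip: both female height bands are given as above 159 cm. Nothing shows that strata were actually scored on a daily total. This stands, and it makes the harm conditional. It does not remove the contradiction, because this is the only operational definition shown and an assessor following it would score on it.

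**A reader might infer that nearly every participant would score the component.** The document does not support that. It gives no expenditure distribution, and sports and other leisure activities count as well as walking. Many is defensible; nearly all is not.

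**A reader might infer that even the hardest exercise programme could not reach the cut-off.** Five 60-minute walks at 3.5 MET average 4.29 × 60 × 5/7 = 184 kcal/day for the 70 kg man and 3.675 × 60 × 5/7 = 158 for the 60 kg woman. But Table 3 gives Program D "Week 9–10: 50–70 min Week 11–12: 50–70 min". At 70 minutes, 80 kg and 4 MET the average is 5.6 × 70 × 5/7 = 280, above the female cut-off. Strength and balance work is also left out of that sum. I put no weight on this benchmark.

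**A reader might infer that a weekly total is the only possible reading.** Without a distribution, no period can be shown to give a 20th percentile. The arithmetic favours a weekly total but does not establish it.

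**The activity exclusion.** The protocol also excludes people with "physical activity or physical therapy in the last 6 months". Read literally, those who remain have little countable activity and might score this component under either period. So the number who would change stratum cannot be stated.

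**Validity.** Allocation is 1:1 within each frailty group, so misclassification does not bias the treatment comparison. This stands in full.

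**Conclusion.** The point holds as an internal contradiction in a stratum-defining threshold. Under the stated formula the printed period implies roughly one to two hours of leisure activity every day (68–146 minutes for men, 48–103 for women, on assumed weights of 60–80 kg and intensities of 2.5–4 MET). That is hard to square with the lowest fifth of older people. The 7-fold gap between a daily and a weekly reading is exact and rests on no assumption.

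The consequence depends on the printed text having been applied. In that case the strata hold different people from those named and robust recruitment is harder, by an amount that cannot be calculated from the document. The harm is to what stratum-specific results describe, not to the randomised comparison within strata. It should be corrected, because the classification precedes and structures the randomisation.

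**What to change.** 1. Reconcile the period, the energy unit (cal or kcal) and the quintile statement against the phenotype source the protocol cites. The sponsor should confirm whether a weekly total was meant.
2. State the period that the questionnaire minutes cover, and that the total is converted to the period of the cut-off before scoring.
3. Confirm which cut-off was used to form the strata.
4. If it was the daily one, re-score from the stored baseline questionnaires. Keep the stratum used at randomisation for the primary analysis, report results by corrected baseline frailty status alongside it, and give the number reclassified in each direction.

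Cost: a one-line correction, plus re-scoring of data already collected if the daily rule was used. The downside is some loss of the 22/22 balance in the re-scored groups and unequal group sizes, so those results will be less precise than planned. Corrected status is still a baseline characteristic, so comparing arms within it remains legitimate.
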